Intubation is a procedure that is difficult to learn and is associated with adverse effects, both short (e.g. pain, hypoxaemia, bradycardia, oropharyngeal trauma) and longer-term (e.g. chronic lung disease, subglottic stenosis). This has led many clinicians to investigate alternative methods of surfactant delivery. Giving nebulised surfactant to spontaneously breathing infants has met with limited success. Progress has been slow due to the technical difficulties encountered in aerosolising such large molecules, the expense of the equipment needed to do so and the expense of the large amount of surfactant needed to form an aerosol. Interest has thus largely focussed on less-invasive methods of surfactant administration. The “minimally invasive” techniques have involved introducing either a feeding tube or vascular catheter into the trachea of a spontaneously breathing infant under direct vision with a laryngoscope. These techniques may reduce the need for mechanical ventilation among preterm infants. However, they appear more difficult than intubation and the many short-term adverse effects of intubation that are due to laryngoscopy are not avoided. Direct administration of surfactant into the pharynx of human infants has been described in randomised studies and prospective cohort studies. It is apparently effective and is an easier technique to perform than endotracheal intubation or passing a feeding tube or vascular catheter into the trachea.

We will perform a study to establish whether giving preterm infants surfactant into their oropharynx at birth reduces their need for subsequent intubation in the first 5 days of life.

The population to be studied include infants born at less than 29 weeks by best obstetric estimate where the treating physician intends to offer intensive care.

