**Figure 1: Study Schema**

[figure not shown]

Prior to delivery a member of the research team or other senior doctor will approach parent(s)/guardian(s) of eligible infants to inform them about the study. Randomisation will occur at delivery. Infants will then be monitored for the duration of their hospitalisation, looking at a large number of secondary outcomes. Subjects' participation will be from time of birth until discharge from hospital.

Infants in the treatment arm will receive oropharyngeal surfactant immediately after birth and then be stabilised on CPAP. Infants in the control arm will be stabilised on CPAP immediately after delivery. Infants will then receive standard care, regardless of their group assignment. Enrolled infants will be intubated for persistent apnoea and/or bradycardia in the DR, or for respiratory failure in the NICU as specified in the protocol. Should infants in either group meet the criteria for respiratory failure following initial randomisation, they will be intubated and surfactant will be administered for treatment of RDS, irrespective of group assignment (i.e. whether or not they have previously received oropharyngeal surfactant). Further surfactant administration and all other aspects of neonatal intensive care will be at the discretion of the treating physicians.

All babies in both groups will be closely watched to see if they need extra treatment for their RDS at any stage, including surfactant given endotracheally. The babies will be treated equally and given whatever treatment is necessary, whether or not they have already been given surfactant into the oropharynx.

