### OROPHARYNGEAL SURFACTANT GROUP

Infants randomised to oropharyngeal surfactant will receive a dose of surfactant (Curosurf, Chiesi Farmaceutici, Parma, Italy) (18) immediately after birth, ideally before the cord is clamped e.g. 60 seconds. If it is given after the cord is clamped it will be given once the infant is placed on the resuscitaire. It will be given within 5 minutes of birth in all cases.

The surfactant will be warmed prior to being drawn up in a sterile syringe as per manufacturer's recommendation. This will be done by opening the mouth gently and administering the surfactant as a single bolus into the oropharynx using a syringe without a needle attached. This will be done as soon as possible after delivery, ideally before the umbilical cord has been clamped.

The dosing recommendations for initial treatment with Curosurf when given by endotracheal tube are:

- 200mg/kg for established RDS
- 100 – 200mg/kg for prophylaxis

One or two further doses of 100mg/kg Curosurf may be given to infants who have persistent respiratory distress despite treatment with surfactant (maximum recommended dose 400mg/kg).

The timing or dosage of ET surfactant will not be affected by initial oropharyngeal surfactant. If an infant is felt to need ET surfactant following initial oropharyngeal administration, then they will receive the standard initial dose of 200mg/kg via ETT.

Infants in our study will not be weighed prior to enrolment. The 50th centile for birth weight (BW) for boys and girls according to gestational age (GA) is shown below

| GA (weeks) | Gr s BW (kg) | Boys BW (kg) |
|------------|--------------|--------------|
| 23         | 0.550        | 0.600        |
| 24         | 0.650        | 0.700        |
| 25         | 0.775        | 0.800        |
| 26         | 0.850        | 0.900        |
| 27         | 0.975        | 1.050        |
| 28         | 1.100        | 1.150        |

In our study, infants < 26 weeks will receive a full 120mg vial of Curosurf. We estimate that this will provide dosing in the therapeutic range as indicated below:

| GA (weeks) | Gr s BW (kg) | Dose (mg/kg) | Boys BW (kg) | Dose (mg/kg) |
|------------|--------------|--------------|--------------|--------------|
| 23         | 0.550        | 218          | 0.600        | 200          |
| 24         | 0.650        | 185          | 0.700        | 171          |

|    |       |     |       |     |
|----|-------|-----|-------|-----|

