1. Bradycardia, hypotension, hyperoxia, cyanosis, apnoea, oxygen desaturations  
These events frequently occur several times per day in this population, whether or not they have received surfactant. Most often these events are short in duration and not of clinical significance. Regular reporting of these adverse events in the CRF is not required.
2. Intracranial haemorrhage  
Some degree of intracranial haemorrhage is detected in  $\geq 30\%$  of infants in this population, whether or not they have received surfactant. Regular reporting of these adverse events in the CRF is not required. All enrolled infants are being screened for intracranial haemorrhage; it is being recorded in the CRF and measured as a secondary outcome.
3. Bronchopulmonary dysplasia  
Bronchopulmonary dysplasia occurs in up to  $\geq 50\%$  in this population of infants, whether or not they have received surfactant. Regular reporting of these adverse events in the CRF is not required. All enrolled infants are being screened for bronchopulmonary dysplasia; it is being recorded in the CRF and measured as a secondary outcome.
4. Pneumothorax, pulmonary haemorrhage  
These are rare events in this population of infants, whether or not they have received surfactant. Regular reporting of these adverse events in the CRF is not required. All enrolled infants are being screened for pneumothorax and pulmonary haemorrhage; it is being recorded in the CRF and measured as a secondary outcome.
5. Endotracheal intubation complication  
Endotracheal intubation complication is not relevant as we are not giving surfactant via this route of administration as the intervention arm for this study. Regular reporting of these adverse events in the CRF is not required.

Only AEs which are not directly associated to the underlying condition of extreme prematurity should be reported. The following information will be recorded: description, date of onset and end date, severity, assessment of relatedness to the study medication, other suspect medication or device and action taken. Follow-up information should be provided as necessary.

AEs considered related to the study medication as judged by an investigator or the sponsor will be followed until resolution or until the event is considered stable. All related AEs that result in a subject's withdrawal from the study or are present at the end of the study, should be followed up until a satisfactory resolution occurs.

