#### **14.6 Safety analysis**

Adverse events following administration of oropharyngeal surfactant will be documented e.g. bradycardia, desaturation. Should an infant require endotracheal intubation for respiratory failure, the intubation difficulty and attempts after oropharyngeal administration of surfactant will also be recorded.

Safety analyses will be carried out on patients in the Safety Set, the definition of which will be finalized in the Statistical Analysis Plan (SAP).

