## 1.3 Endpoints

### Primary endpoint

The primary endpoint is the incidence of endotracheal intubation for respiratory failure within 120 hours of birth.

Enrolled infants will be intubated for persistent apnoea and/or bradycardia in the DR, or for respiratory failure in the NICU defined as  $\geq 2$  of:

- Clinical signs – worsening tachypnoea; grunting; subcostal, intercostal and/or sternal recession
- Acidosis – pH < 7.2 on 2 blood gases (arterial or capillary)  $\geq 30$  minutes apart
- $O_2$ -FiO2 > 0.4 to keep SpO2  $\geq 90\%$  for > 30minutes
- PCO2 > 9.0 kPa on 2 blood gases (arterial or capillary)  $\geq 30$  minutes apart
- Apnoea – recurrent apnoea treated with mask ventilation

The frequency of blood gas monitoring is based on the clinical decision of the treating physician, as per routine practice.

|         |                                           |              |              |
|---------|-------------------------------------------|--------------|--------------|
| UCD CRC | SAP for the POPART trial                  |              |              |
| UCD CRC | Template: Statistical Analysis Plan (SAP) | Version: 1.0 |              |
|         |                                           |              | Page 5 of 19 |

Enrolled infants will only be intubated if they reach the pre-determined criteria for respiratory failure. Attending clinicians may give endotracheal surfactant via a thin catheter (LISA technique) or via an endotracheal tube (ETT). After giving endotracheal surfactant for the treatment of RDS, attending clinicians may attempt to extubate the babies immediately ("INSURE") or they may elect to ventilate the babies for a longer period. This is at their discretion.

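### Protocol 13.3 item 5 waives routine reporting of intubation complications for a reason the care pathway contradicts, leaving non-serious complications and NICU intubation attempts with no required two-arm capture

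*Combined protocol and SAP*

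**What the plan says.** Protocol 13.3 lists the reactions in the product information and then names groups of events that need not be reported as AEs, on the ground that they are directly related to extreme prematurity. Item 5 covers complications of intubation: "Endotracheal intubation complication is not relevant as we are not giving surfactant via this route of administration". The sentence goes on to limit this to the intervention arm's treatment, and the item ends as the others do: "Regular reporting of these adverse events in the CRF is not required".

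Other sections bear on the same events:

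- Protocol 11.1, below Figure 1, on infants in either group who meet the failure criteria: "they will be intubated and surfactant will be administered for treatment of RDS, irrespective of group assignment".
- Protocol 11.1, oropharyngeal surfactant group, on infants who need tracheal surfactant after the study dose: "then they will receive the standard initial dose of 200mg/kg via ETT". SAP 1.3 also allows a thin catheter, so tracheal surfactant does not always mean a tube.
- Protocol 9.1, on why other routes are sought: "Intubation is a procedure that is difficult to learn and is associated with adverse effects". Its examples include hypoxaemia, bradycardia, oropharyngeal trauma and subglottic stenosis. Protocol 9.2 adds tube blockage as a side effect of the product.
- Protocol 11.3.2 (safety assessment) records delivery-room intubation attempts after the study dose. Protocol 14.6 goes further: "the intubation difficulty and attempts after oropharyngeal administration of surfactant will also be recorded".
- SAP 5.4 lists the safety tables. None concerns intubation difficulty, attempts or complications.

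**The concern.** The reason given for item 5 is the route of the randomised dose. That route does not decide whether an infant in this trial is intubated: intubation is the primary event and can occur in either arm. Nor does item 5 meet the test set in its own section, since the product table places this reaction among procedural complications and not among the effects of prematurity. Items 2 to 4 point to a secondary outcome that records the same event. Item 5 points to nothing.

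Two questions are at stake. The trial's rationale is that fewer intubations means less harm from intubation, which calls for a count of that harm by arm. And a volume of up to 3 mL placed in the oropharynx could make a later intubation harder, which calls for the same count among intubated infants with a control comparison. A rule that does not require the events to be recorded limits what the trial can say on either.

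**Working it through.** **1. What is captured, and where**

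| Event | Required capture | Both arms? |
|---|---|---|
| Attempts, delivery room | Secondary outcome (Protocol 10.3, SAP 1.3), analysed among infants intubated there (SAP 5.1.1) | Yes |
| Attempts, NICU | Protocol 14.6 only | No: worded for infants given oropharyngeal surfactant |
| Intubation difficulty | Protocol 14.6 only | No, as above; no table in SAP 5.4 |
| Oropharyngeal trauma, tube blockage, subglottic stenosis, if not serious | None; item 5 waives routine reporting | No |
| Bradycardia or desaturation at intubation | Routine reporting waived by item 1 as well | No |
| Chronic lung disease, pneumothorax | Secondary outcomes | Yes |
| Death, important medical event | SAE report (Protocol 13.4) | Yes |

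The gap is rows 2 to 5. The safety set (Protocol 14.3, SAP 3.2.3) keeps all control infants for comparison, so a two-arm safety analysis was intended.

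**2. How many infants it concerns**

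Inputs from Protocol 14.2: 46% control, 28% surfactant, two-sided 5%, 80% power, 224 raised to 250. Allocation is 1:1 (Protocol 11.3.6).

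Reproducing the plan's figure with the pooled two-proportion formula, mean rate 0.37:

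n per arm = [1.960 × √(2 × 0.37 × 0.63) + 0.842 × √(0.46 × 0.54 + 0.28 × 0.72)]² / 0.18² = 111.75, so 112 per arm and 224 in all, as stated. 224 / 0.9 = 248.9, so 249 against the stated 250.

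Infants intubated within 120 hours, at 125 per arm:

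- Planning rates: 125 × 0.46 = 57.5 and 125 × 0.28 = 35; together 92.5 of 250 (37%).
- No treatment effect, over the 46–60% range in Protocol 14.2: 250 × 0.46 = 115 to 250 × 0.60 = 150.

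**3. Break-even**

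The share of all randomised infants with a complication is the intubation rate times the rate per intubated infant. With r_C and r_S for the latter in the control and surfactant arms, the surfactant share is larger when 0.28 × r_S > 0.46 × r_C, that is, when r_S / r_C > 0.46 / 0.28 = 1.64. This needs no assumed complication rate. With a 60% control rate and the same 18-point effect it is 0.60 / 0.42 = 1.43. With no effect on intubation it is 1.

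**4. What a comparison could show**

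The documents give no complication rate, so the rates below are assumptions, equal per intubated infant in both arms, at 125 per arm.

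| Assumed rate | Control | Surfactant | Two-sided p at these counts | Approximate power |
|---|---|---|---|---|
| 10% | 5.75 | 3.5 | 0.45 | 12% |
| 20% | 11.5 | 7.0 | 0.28 | 19% |
| 40% | 23 | 14 | 0.11 | 36% |

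If the rate were 20% in controls and doubled to 40% in the surfactant arm, the counts would be 11.5 and 14 (p about 0.60, power about 8%). A table by arm would describe; it could not settle the question.

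**The case against.** The strongest reply has four parts.

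- Item 5 is limited to the randomised treatment, and it is true that this is not given through a tube. That stands as a reading of the sentence. It does not justify the waiver, because the study dose can bear on a later intubation and Protocol 11.3.2 and 14.6 say so in effect.
- Much is measured. A reader might infer that the harm the trial seeks to avoid and the harm the dose might cause both go unrecorded. The documents do not support that: delivery-room attempts are compared in both arms, chronic lung disease and pneumothorax are outcomes, and Protocol 14.6 promises difficulty and attempts after the dose. A reader might also infer that the DSMB would see no intubation complications. That is not supported either: important medical events and deaths remain reportable within 24 hours, and the DSMB reviews adverse events in both groups (Protocol 13.5). What it would lack is routine reports of the non-serious ones.
- A large effect of the dose on intubation is not shown. The dose is due within 5 minutes of birth, while the gas and oxygen criteria for NICU failure take at least 30 minutes, so any direct effect is most plausible in the delivery room, where attempts are already compared. This stands, and nothing in the documents supports a particular increase. It is a reason to measure, not evidence of harm.
- Low power and late timing limit the remedy. Both stand. The table would be descriptive. Version 2.1 (November 2020) records close-out at some sites, and the SAP is dated April 2022. The CRF is not among the documents, so what it actually collected at intubation cannot be checked.

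**Conclusion.** The concern holds in limited form. The reason given in item 5 conflicts with Protocol 11.1, 11.3.2 and 14.6, and those sections must be reconciled. Followed as written, the plan requires no two-arm record of non-serious complications such as oropharyngeal trauma and tube blockage, or of NICU intubation attempts. The difficulty item in Protocol 14.6 has no control counterpart and no table in SAP 5.4.

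About 92 of 250 infants fall within the waiver's scope at the planning rates, and 115 to 150 if there is no effect and the rate is 46–60%. These counts assume 125 infants per arm. The 1.64 break-even depends only on the planning intubation rates; whether the dose raises the complication rate at all is unknown.

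This is a gap in safety data. It does not touch the primary analysis, the type I error rate or the sample size.

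**What to change.** 1. Remove the item 5 waiver and reconcile Protocol 13.3 with 11.1, 11.3.2 and 14.6. Word the 14.6 item for both arms.
2. At each intubation in both arms, record difficulty, number of attempts, and complication (yes/no and type). Include desaturation or bradycardia during intubation, which item 1 would otherwise still exclude.
3. In SAP 5.4, add a descriptive table by arm: infants with at least one intubation complication over all randomised infants, with a supplement per intubated infant. The first keeps the randomised comparison. The second conditions on an event after randomisation and should be labelled so. Present the table whatever the frequency, since the present rule in SAP 5.4 describes non-serious events by arm only above 5% in either arm.
4. Give the same table to the DSMB.
5. Where sites have closed and the data cannot be collected, tabulate by arm what was recorded and state the missing complication data as a limitation.

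The cost is a wording change, a short CRF entry at an event already recorded, and one table. The downside is slightly more data entry.

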#### Blinding

This is an open-label study. The study will not be blinded to investigator, subjects, or medical or nursing staff. We are not using a placebo, and in the event of the baby being randomised to the ‘CONTROL’ arm, then they will be commenced on CPAP immediately after birth.

The trial statistician will be blinded for data analysis, and will be kept unaware of treatment group assignments. The randomization schedule will be drawn up by an independent statistician, to facilitate this.

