## 13.3 Reporting procedures for all adverse events

The investigational medicinal product (IMP), Curosurf, is licensed for use for prevention and treatment of respiratory distress syndrome (RDS) in premature infants in Europe for more than 25 years. It is given as a single dose by the endotracheal route and may on occasion be repeated. It has an excellent safety profile.

Many of the adverse events which are listed in the Summary of Product Characteristics for Curosurf (portactant alfa) below occur commonly in preterm infants who are admitted to the Neonatal Intensive Care Unit (NICU), whether or not they have received surfactant. Others are seen infrequently in this population, whether or not they have received surfactant.

| System organ Class                              | Adverse Reaction                     | Frequency |
|-------------------------------------------------|--------------------------------------|-----------|
| Infections and infestations                     | Sepsis                               | Uncommon  |
| Nervous system disorders                        | Haemorrhage intracranial             | Uncommon  |
| Cardiac disorders                               | Bradycardia                          | Rare      |
| Vascular disorders                              | Hypotension                          | Rare      |
| Respiratory, thoracic and mediastinal disorders | Bronchopulmonary dysplasia           | Rare      |
|                                                 | Pneumothorax                         | Uncommon  |
|                                                 | Pulmonary haemorrhage                | Rare      |
|                                                 | Hyperoxia                            | Not known |
|                                                 | Cyanosis neonatal                    | Not known |
| Investigations                                  | Apnoea                               | Not known |
|                                                 | Oxygen saturation decreased          | Rare      |
|                                                 | Electroencephalogram abnormal        | Not known |
| Injury, poisoning and procedural complications  | Endotracheal intubation complication | Not known |

AEs that are directly related to the underlying condition of extreme prematurity do not need to be reported as an AE on this study, for example:

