It will be left to the investigator's clinical judgment whether or not an AE is of sufficient severity to require the subject's removal from the study. If this occurs, the subject must undergo an end-of-study assessment and be given appropriate care under medical supervision until symptoms cease or the condition becomes stable.

The severity of events will be assessed on the following scale: mild, moderate, severe.

The relationship of AEs to the study medication will be assessed by the investigator.

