### 13.5 Data Safety Monitoring Board (DSMB)

A DSMB will be established to perform ongoing safety surveillance and to perform interim analyses on the study data. The DSMB will be an independent committee, composed of a minimum of three members; at least two will be clinicians not involved in the trial but with experience and expertise in clinical trials; at least one member will be a clinician with expertise in neonatology. Each member will state that they have no conflict of interest with the sponsor or company involved in the study or any other conflicting interest to declare.

The DSMB will meet on a 6-monthly basis after start of the trial and will review the frequency and severity of adverse events in both treatment groups. If they observe any significant excess of serious adverse events in the intervention group associated with the intervention, they may recommend premature termination of the trial on the basis of serious safety concerns.

The DSMB will also conduct interim analysis to determine whether the data provide overwhelming evidence of efficacy or futility, defined as a highly statistically significant difference (i.e.  $P < 0.001$ ) in the primary outcome or a highly statistically significant difference in the important secondary outcome of death before hospital discharge. Interim analysis for efficacy or futility will be carried out after approximately 50% of participants ( $n=126$ ) have completed the study. The DSMB may recommend early termination of the trial due to efficacy or futility.

The advice(s) of the DSMB will be notified upon receipt by the sponsor to the REC and CA that approved the protocol. With this notification a statement will be included indicating whether the advice will be followed.

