##### **Adverse events**

The number of adverse events (i.e. all events occurring, worsening or becoming serious after the randomisation), and the number and percentage of infants reported as having at least one emergent adverse event, will be reported by system organ class and preferred term, for each treatment group.

The same description will be performed for serious adverse events (SAE), severe AE, AE treatment related and AE leading to IMP withdrawal.

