#### 5.4 Safety evaluation

Adverse events will be summarized for each site and for the whole sample, including:

- Total number of adverse events
  - Number and percentage of adverse events that were serious (SAES)
  - Number and percentage of adverse events that were mild, moderate and severe
  - Number and percentage of treatment-related adverse events
  - Number and percentage of adverse events that were resolved without sequelae, resolved with sequelae, ongoing, or resulted in death.
- Number of deaths (all causes) per treatment arm
- Number of deaths resulting from adverse events per treatment arm
- Number and percentage of subjects experiencing
  - Any adverse event
  - Any serious adverse event
  - Mild, moderate and severe adverse events
  - Treatment-related adverse events

Further, any non-serious adverse event occurring with a greater than 5% frequency in either treatment arm, will be described by treatment arm, including:

- System organ class
- Event term
- Number of subjects per treatment arm affected by the event
- Total number of events of this type that occurred per treatment arm

For all serious adverse events (SAEs), the above information will be reported as well as:

- Number of these SAEs causally related to treatment, per treatment arm
- Number of these SAEs with fatal outcome, per treatment arm
- Number of treatment-related SAEs of this type with fatal outcome

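### Whether an unlisted adverse event is recorded depends on an arm-aware judgement about prematurity, which puts the by-arm adverse-event tables at risk of uneven capture

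*Combined protocol and SAP*

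**What the plan says.** Protocol 13.3 reproduces the product-information table of adverse reactions and then exempts events that stem from prematurity itself. Five numbered groups follow, introduced as examples, and the section then states the general rule: "Only AEs which are not directly associated to the underlying condition of extreme prematurity should be reported". It gives no criteria for that judgement, names nobody to make it, and provides no blinded review. On drug causality it says: "The relationship of AEs to the study medication will be assessed by the investigator".

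The Blinding paragraph under 11.3.6 says: "The study will not be blinded to investigator, subjects, or medical or nursing staff". Controls receive no placebo.

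The resulting counts are used by arm in three places:
- Protocol 14.6: adverse-event numbers "will be reported by system organ class and preferred term, for each treatment group", defined there as everything that occurs, worsens or becomes serious after randomisation.
- Protocol 13.5: the DSMB "will review the frequency and severity of adverse events in both treatment groups".
- SAP 5.4: "any non-serious adverse event occurring with a greater than 5% frequency in either treatment arm, will be described by treatment arm". Serious events and all-cause deaths are also given by arm. No test is specified.

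**The concern.** Causality should be judged after an event is on record. Here a causal judgement decides whether the event enters the record at all, and those who report know the arm. In a control infant prematurity is the natural explanation, so the event tends to drop out. In a treated infant the bolus is a second candidate cause. That may prompt a report, or staff who trust the drug may still blame prematurity. If the two arms are filtered differently, the tables reflect attribution habits as well as the drug. They could show an excess that is not real or hide one that is. This matters because the route of administration is unlicensed, and open adverse-event reporting is how unforeseen effects would come to light.

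**Working it through.** The plan gives no figure on this point to reproduce. The check is a reading of the text, followed by an illustration on assumed inputs.

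**1. What is left to judgement.** The table in 13.3 has 13 reaction terms. The five exempt groups cover 6 (bradycardia, hypotension, hyperoxia, cyanosis, apnoea, desaturation) + 1 (intracranial haemorrhage) + 1 (BPD) + 2 (pneumothorax, pulmonary haemorrhage) + 1 (intubation complication) = 11. That leaves 13 − 11 = 2: sepsis and abnormal EEG. Neither is a secondary outcome in protocol 10.3 or SAP 1.3, and the itemised medication list in 12.7 has no entry for treatment of sepsis. Any event that appears neither in the table nor among the outcomes is in the same position.

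**2. Why the judgement can differ by arm.**
- 13.1.1 defines an adverse event in terms of a subject who has been given a medicinal product; controls get no study drug.
- The lowest grade of drug causality in 13.2.2 applies when a link cannot be excluded. That can arise only in the surfactant arm.
- 14.6 says bradycardia and desaturation after oropharyngeal surfactant will be documented, whereas 13.3 says regular reporting of them is not required. If 14.6 were followed in treated infants and 13.3 in controls, capture would differ by design.
- 14.6 also counts all post-randomisation events, which the rule in 13.3 cannot supply.

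**3. What lies outside the filter.** Death, IVH, cystic PVL, BPD, CLD, NEC, treated ROP, pneumothorax and pulmonary haemorrhage are recorded for both arms as outcomes (10.3, SAP 1.3).

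**4. Illustration.** Let r_T and r_C be the fractions of events reported in the treated and control arms. Then

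reported RR = true RR × r_T / r_C.

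The documents give neither fraction; these values are assumptions.

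| True RR | r_T | r_C | Reported RR |
|---|---|---|---|
| 1.0 | 0.5 | 0.5 | 1.00 |
| 1.0 | 0.5 | 0.4 | 1.25 |
| 1.0 | 0.5 | 0.3 | 1.67 |
| 1.0 | 0.5 | 0.2 | 2.50 |
| 1.0 | 0.4 | 0.5 | 0.80 |
| 1.0 | 0.3 | 0.5 | 0.60 |
| 1.5 | 0.3 | 0.5 | 0.90 |

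The result depends on the base level as well as the gap. A 5-point gap gives 0.15/0.10 = 1.50 when few events are reported, but 0.55/0.50 = 1.10 when about half are.

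**5. Equal filtering.** If r_T = r_C the ratio is unbiased and only events are lost. Even so, a true risk of 10% in both arms with 30% reported shows as 0.10 × 0.30 = 3%. That falls below the 5% threshold in SAP 5.4, so the term would not be tabulated.

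**The case against.** A reader might infer that the comparison is biased, or that it will show a false excess with surfactant. The documents do not support that. They establish the conditions for differential capture, but not its occurrence, direction or size. They also do not say who judges association with prematurity: 13.4 names the investigator as reporter and 13.3 gives the investigator the drug-causality call, so that the same person applies the filter is a reasonable inference only.

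Further points on the other side:
- **Most major harms escape the filter.** This stands and sets the scope of the point.
- **Serious events have their own rule.** 13.4 makes death and important medical events reportable, with no prematurity exemption attached to those two criteria, and the DSMB's stated trigger is an excess of serious events. So serious sepsis has a route into the record. This largely stands, although importance is itself a judgement and the text does not settle whether 13.3 also governs serious events.
- **The five groups are exempted by type in both arms.** This stands, except where 14.6 pulls bradycardia and desaturation back in for treated infants.
- **The SAP presentation is descriptive.** Totals are by site and for the whole sample; only deaths, serious events and non-serious events above 5% are by arm. Chances of reaching p<0.05 would therefore describe an unplanned analysis. Descriptive tables and DSMB review can still mislead if capture differs.
- **Filtered events are not lost for ever.** Hospital records are source documents (section 16). This stands, but nothing in the plan calls for them to be searched.
- **Recording everything to discharge is a burden.** This is fair, and it favours a well-chosen exemption list over no exemptions.

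**Conclusion.** The point holds as a risk of differential ascertainment, limited to events outside the five listed groups and the CRF outcomes, and mainly to non-serious ones. Sepsis and abnormal EEG are the clearest cases, being labelled reactions that are neither exempt nor outcomes. It does not extend to death or the main complications of prematurity, nor to the primary endpoint.

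The size is unknown. The risk ratios of 0.60 to 2.50 under no true effect, and 0.90 under a true ratio of 1.5, rest wholly on assumed reporting fractions and serve only to show that distortion can go either way. With equal reporting there is no bias, only loss of information. The conflict between 13.3 and 14.6 rests on no assumption and needs resolving in any case. The change is worth making because it is cheap and removes an avoidable weakness in the safety comparison.

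**What to change.** 1. **Protocol 13.3:** replace the open-ended examples and the attribution sentence with a closed list of exempt event terms, applied identically in both arms. Record any other event whatever its presumed cause, and judge causality only afterwards.
2. **CRF:** add yes/no items for sepsis and abnormal EEG, completed for every infant.
3. **SAP 5.4:** rest the between-arm safety comparison on these items and the existing CRF outcomes. Label the remaining adverse-event counts as filtered by attribution, and describe treatment-related events in the surfactant arm only.
4. **Protocol 13.3 and 14.6:** reconcile the waiver of regular reporting for bradycardia and desaturation with the statement that they will be documented after surfactant, and with the count of all events after randomisation.

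The cost is wording changes and some extra CRF entry at sites; how much depends on the length of the exemption list. No visits or procedures are added. The document history for protocol version 2.1 records that close-out had begun at some sites, and the SAP is later. If data collection is over, item 3 and the reconciliation in item 4 can still be done in the SAP and the report. Items 1 and 2 would then be possible only by searching hospital records in the same way for both arms, which costs more.
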